### Mediation analysis

We hypothesize that the weight loss advantage for those assigned to TECH would be explained (entirely or partially) by TECH’s higher rates of adherence to self-monitoring and attainment of behavioral goals. To test this mediation hypothesis, we will fit a linear mixed model predicting weight loss similar to the model described above, but now including in the regression equation the potential mediating variables corresponding to adherence to self-monitoring. To the extent that adherence mediate the effects of the experimental condition, in the model with adherence included, we expect the coefficient on the treatment group by time interaction variable to be reduced compared to the treatment group by time interaction coefficient from the model without adherence. This difference provides an estimate of the extent to which adherence may mediate the effects of the experimental condition on weight loss. Bootstrapping will be used to estimate the sampling variability of the mediation effect.

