**Methods/design:**

Ninety-six obese adults (BMI 30–39.9 kg/m^2^) will be randomized to one of three treatment conditions: (1) standard behavioral weight loss (STND), (2) technology-supported behavioral weight loss (TECH); or (3) self-guided behavioral weight loss (SELF). All groups will aim to achieve a 7% weight loss goal by reducing calorie and fat intake and progressively increasing moderate intensity physical activity to 175 minutes/week. STND and TECH will attend 8 group sessions and receive regular coaching calls during the first 6 months of the intervention; SELF will receive the Group Lifestyle Balance Program DVD’s and will not receive coaching calls. During months 1–6, TECH will use a specially designed smartphone application to monitor dietary intake, body weight, and objectively measured physical activity (obtained from a Blue-tooth enabled accelerometer). STND and SELF will self-monitor on paper diaries. Linear mixed modeling will be used to examine group differences on weight loss at months 3, 6, and 12. Self-monitoring adherence and diet and activity goal attainment will be tested as mediators.

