### Theoretical framework

The conceptual basis for the ENGAGED study is Carver and Scheier’s control systems theory (CST) of self-regulation
[27]. CST posits that self-regulation can be understood in terms of feedback loops, wherein people: (1) set a goal, (2) self-monitor their current status to identify discrepancy from a goal, and then (3) modify their behavior to reduce perceived discrepancy. From a CST perspective, DPP’s efficacy can be attributed to helping participants (1) set appropriate caloric intake and physical activity goals, (2) self-monitor weight, eating behavior, and activity, and (3) adjust behaviors to reach the targets. According to CST, the core challenge in weight loss is aligning diet and activity with goals. Most weight loss efforts lose because traditional paper and pencil self-monitoring of diet and activity fails to provide salient, timely decision support and accurate feedback.

Using CST as a guiding framework, ENGAGED will develop a persuasive, interactive smartphone application designed improve the saliency, timeliness, and accuracy with which participants receive feedback on their daily dietary and activity goals. Participants will monitor dietary intake and wear a Bluetooth-enabled accelerometer to receive real-time feedback on objectively measured physical activity. Persuasively designed goal thermometers on the application will display current behavior and goals to highlight behavior-goal discrepancies. We posit based on CST that the experience of receiving consistent and immediate feedback from the ENGAGED technology should reinforce adherence to self-monitoring and healthy behavior change, both during and after in-person treatment ends.

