### Study aims

Guided by CST and social networks research, the ENGAGED study will evaluate the feasibility and efficacy of a technology-supported weight loss program for obese adults. Specifically, the primary aim of the ENGAGED study is to conduct a three-group randomized controlled trial testing the efficacy of the ENGAGED technology-supported behavioral weight loss program, as compared to the same program delivered using standard paper and pencil self-monitoring, and self-guided behavioral weight loss supported by participants receiving DVD’s depicting DPP treatment. Primary outcomes include: (1) weight loss and (2) behavioral adherence, which is operationalized by (a) self-monitoring of diet and activity and (b) attainment of diet and activity goals. As a secondary outcome, the time spent administering the intervention by lifestyle coaches will also be examined to assess intervention costs. The second aim of the ENGAGED study is to test whether the weight loss in the technology-supported condition is mediated by behavioral adherence to self-monitoring and achievement of diet and activity goals.

We hypothesize that using a theory-guided, technology-supported weight loss treatment will result in clinically significant weight loss with fewer in-person sessions by preserving regular social support, accountability, and feedback via mobile technology. Further, we hypothesize that technology-supported weight loss treatment will result in greater weight loss compared to the traditional paper self-monitoring approach.

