#### Dietary intake adherence

Dietary intake will be assessed at baseline, 3-, and 6-months via interview by a non-intervention registered dietician using the computer-assisted telephone interview (CATI) 24 hour recalls
[37] using the multiple pass method to assess calorie and fat intakes. At each time point, three days (one weekend and two weekdays) will be randomly selected over a three week period to conduct the recalls. The data derived from the recalls will be analyzed using the annually updated University of Minnesota Nutrition Coordinating Center’s (NCC) Nutrition Data System for Research (NDS-R-2005). Only STND and TECH will complete dietary recalls at 3- and 6-months.

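### The mediation model enters only self-monitoring variables, although aim 2, the abstract and the section's own hypothesis also name goal attainment as a mediator

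*Protocol article*

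**What the plan says.** All places are in the protocol article.

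- **Study aims.** The second aim asks whether weight loss in TECH is "mediated by behavioral adherence to self-monitoring and achievement of diet and activity goals". The same section states that behavioral adherence is "operationalized by (a) self-monitoring of diet and activity and (b) attainment of diet and activity goals".
- **Abstract, Methods/design.** "Self-monitoring adherence and diet and activity goal attainment will be tested as mediators".
- **Mediation analysis, first sentence.** The TECH advantage is expected to be explained by "TECH’s higher rates of adherence to self-monitoring and attainment of behavioral goals".
- **Mediation analysis, model sentence.** The model for that hypothesis is the weight-loss mixed model, now "including in the regression equation the potential mediating variables corresponding to adherence to self-monitoring".
- **Mediation analysis, estimate.** The drop in the group-by-time coefficient is the mediation measure: "This difference provides an estimate of the extent to which adherence may mediate the effects of the experimental condition on weight loss". Its variability is to be bootstrapped.
- **Linear mixed modeling.** Goal attainment at 3 and 6 months appears as an outcome, listed separately from behavioral adherence.
- **Dietary intake adherence.** "Only STND and TECH will complete dietary recalls at 3- and 6-months". The Physical activity adherence section states no such limit by arm.

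**The concern.** The hypothesis and the model meant to test it stand next to each other in one section and do not match. An analyst who follows the model sentence would enter the self-monitoring variables, compare coefficients and stop. Goal attainment would then have no mediation estimate, and that part of aim 2 would go unanswered.

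The result could also mislead. If TECH changes what people eat or how active they are without changing how often they record, a model containing only recording frequency leaves that effect in the treatment coefficient. A report could then say that behavioral adherence explains little of the TECH effect, when only one of its two components had been examined. The Theoretical framework section makes such a path plausible: the application is meant to improve the "saliency, timeliness, and accuracy with which participants receive feedback on their daily dietary and activity goals", which can alter behavior on the same number of recorded days.

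**Working it through.** **1. Mediators stated, place by place**

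| Place | Self-monitoring | Goal attainment |
|---|---|---|
| Abstract, Methods/design | yes | yes |
| Study aims, aim 2 | yes | yes |
| Mediation analysis, hypothesis | yes | yes |
| Mediation analysis, model sentence | yes | no |

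No other mediation model is described.

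**2. Can self-monitoring stand in for goal attainment?** Not by its definition. A diet day earns full credit once at least 1000 calories and 25 g of fat are recorded. Both are floors without a ceiling, so a day recorded well above the assigned goals counts as fully adherent. For TECH, an activity day counts if the accelerometer was worn for at least 8 hours, whatever activity it registered. The scores measure recording and wear, not whether goals were met.

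**3. How much could be left unexplained?** The documents give no path coefficients, so this step is an illustration on assumed values. Let T be treatment (TECH vs STND), M1 self-monitoring, M2 goal attainment and Y weight loss. The paths are T→M1 = a1, T→M2 = a2, M1→M2 = d, M1→Y = b1 and M2→Y = b2, with no direct effect of T on Y. In linear models:

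- total effect = a1·b1 + (a2 + a1·d)·b2
- coefficient of T with M1 only in the model = a2·b2
- coefficient of T with M1 and M2 in the model = 0

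| Assumed pathway | a1, d, a2, b1, b2 | Total | Left with M1 only | Share left |
|---|---|---|---|---|
| Serial: T→M1→M2→Y | 0.7, 0.7, 0, 0, 0.7 | 0.7·0.7·0.7 = 0.343 | 0·0.7 = 0 | 0% |
| Two equal parallel paths | 0.7, 0, 0.7, 0.5, 0.5 | 0.35 + 0.35 = 0.70 | 0.7·0.5 = 0.35 | 50% |
| Mixed | 0.7, 0.35, 0.35, 0, 0.7 | (0.35 + 0.245)·0.7 = 0.4165 | 0.35·0.7 = 0.245 | 59% |
| Goal attainment changed independently of self-monitoring | 0.7, 0, 0.7, 0, 0.7 | 0.7·0.7 = 0.49 | 0.7·0.7 = 0.49 | 100% |

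A simulation with 400,000 subjects agreed. With M1 only, the remaining coefficients were -0.002, 0.356, 0.241 and 0.488 (in table order), or -1%, 50%, 59% and 100% of the simulated totals. With both mediators entered, the remaining coefficient was between -0.002 and 0.006 in all four cases.

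**4. Is the missing mediator available?** Yes, for the comparison that matters here. Recalls are taken in TECH and STND at 3 and 6 months. Accelerometer activity is measured at the same visits with no arm excluded. Only dietary goal attainment in SELF is unavailable at follow-up.

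**The case against.** The strongest reply is that the test has not been dropped. The abstract promises it, and the model is introduced as the test of a hypothesis that includes goal attainment. The sentences defining the estimate speak only of adherence, which the Study aims section defines to cover both components. On that reading the model sentence is loosely worded in a condensed article.

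Part of this stands. A reader might infer that the sponsor decided to leave goal attainment out; the abstract and the hypothesis do not support that. But the broad reading does not repair the model sentence. That sentence limits the variables to self-monitoring, and both the Mediation analysis hypothesis and the Linear mixed modeling section list adherence and goal attainment as separate things.

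A second reply concerns the consequence. A reader might infer that any TECH effect through better eating or activity would be reported as unmediated. That is too strong. The Theoretical framework section describes a loop in which self-monitoring reveals a gap from the goal and behavior then changes. An effect following that sequence would be credited to self-monitoring, with nothing left over.

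A third stronger reading is that goal attainment as a whole cannot enter a three-arm model. The documents support this only for the diet measure.

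**Conclusion.** The contradiction is established from the text alone and needs no assumption. As written, the model does not estimate mediation by goal attainment, which aim 2 requires.

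The effect on the mediated share is conditional and unknown. Only the part of a TECH effect that bypasses self-monitoring would be left unexplained: anywhere from 0% to 100% in the cases above. Those figures assume linear paths, no direct effect of TECH on weight, no confounding of mediator and outcome, and mediators measured without error. They show the possible range and do not predict the result. The point concerns the second aim; the primary weight-loss comparison is unaffected.

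**What to change.** In the model sentence of the Mediation analysis section, name diet goal attainment (from the recalls) and activity goal attainment (from the accelerometer) as mediators alongside self-monitoring. Define the coefficient difference and its bootstrap on that model. Assess the diet goal mediator, and any joint model that contains it, in TECH vs STND; activity goal attainment needs no such restriction on the stated data collection. If a model with self-monitoring alone is also reported, label it mediation by self-monitoring, not by behavioral adherence overall. Settle the wording before any mediation result is seen, so that the mediator set is not chosen afterwards.

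The change needs no new data. Its cost is precision: the mediators are likely to be correlated, and the plan expects about 30 participants per arm at the final endpoint, so estimates from a joint model will be less precise.

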## Methods

### Study design

The research design is a 3 × 4 factorial with one between subjects factor (treatment condition) with three levels and one within subjects factor (time) with four levels (baseline, 3-, 6-, and 12-months). Participants will be randomized to one of three groups: a) Standard behavioral weight loss program (STND); b) technology-supported behavioral weight loss program (TECH); or c) self-guided behavioral weight loss program (SELF).

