#### Weight loss

We measure weight loss at 3, 6, and 12 months. Using data from a previous weight loss trial
[16], we saw standard deviations of 8.4 and 10.7 pounds at months 3 and 6, respectively, with a correlation of 0.86 between the two time points. With 80% power and an n=30 in both groups, we will be able to detect a difference of 6.6 pounds between the two groups.

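### The mediation model enters only self-monitoring adherence although goal attainment is also a named mediator, and its interaction criterion misses a constant mediated effect if the outcome is weight loss at follow-up

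*Protocol article*

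**What the plan says.** **Mediators.** Under Study aims, the second aim is to test whether weight loss in TECH is "mediated by behavioral adherence to self-monitoring and achievement of diet and activity goals". The abstract (Methods/design) agrees: "Self-monitoring adherence and diet and activity goal attainment will be tested as mediators". The section Mediation analysis opens with the same pair, attributing TECH's expected advantage to its "higher rates of adherence to self-monitoring and attainment of behavioral goals". The sentence that builds the model then adds only "the potential mediating variables corresponding to adherence to self-monitoring".

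**Criterion.** The section states: "we will fit a linear mixed model predicting weight loss similar to the model described above". It compares that model with and without adherence and says "we expect the coefficient on the treatment group by time interaction variable to be reduced compared to the treatment group by time interaction coefficient". The difference is the estimate of mediation, with bootstrapping for its sampling variability.

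**Time and outcome.** Study design describes "one within subjects factor (time) with four levels (baseline, 3-, 6-, and 12-months". The power section on weight loss says "We measure weight loss at 3, 6, and 12 months". Linear mixed modeling treats time as nominal, makes treatment group the main independent variable, and adds group-by-time interactions to see whether change over time differs by group.

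**The concern.** There are two separate problems.

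1. The aim, the abstract and the hypothesis name two kinds of mediator, and the model contains one. An analyst who follows the model sentence leaves part of the second aim untested.
2. An interaction with nominal time measures how the treatment effect differs from its value at the reference time. If the reference is a follow-up visit, a steady TECH advantage lies in the group term and not in the interaction. A drop in the interaction then says nothing about whether adherence explains that advantage, and the analysis could report no mediation when mediation is complete. If the reference is baseline, the criterion can work. The article does not fix which applies, nor how adherence enters.

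**Working it through.** **Step 1. Mediators named against mediators entered.**

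| Place in the protocol article | Self-monitoring | Goal attainment |
|---|---|---|
| Abstract, Methods/design | yes | yes |
| Study aims, second aim | yes | yes |
| Mediation analysis, hypothesis | yes | yes |
| Mediation analysis, model sentence | yes | no |

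Study aims uses behavioral adherence as an umbrella for both kinds. The model sentence is narrower, so the umbrella term does not cover the gap.

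**Step 2. Which model lies behind the power figure.** The inputs (Sample size and power, Weight loss) are SDs of 8.4 and 10.7 lb at months 3 and 6, correlation 0.86, 30 per group, 80% power and a stated detectable difference of 6.6 lb. Two-sided alpha of 0.05 is my assumption; that section gives none.

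- Group effect averaged over months 3 and 6: SD = √[(8.4² + 10.7² + 2 × 0.86 × 8.4 × 10.7)/4] = 9.215 lb. Detectable difference = (1.960 + 0.842) × 9.215 × √(2/30) = 6.67 lb. Power at 6.6 lb is 79.2%.
- Group-by-time effect, month 6 minus month 3: SD = √(8.4² + 10.7² − 2 × 0.86 × 8.4 × 10.7) = 5.52 lb. Detectable difference = 3.99 lb.
- Single visits: 6.08 lb at month 3, 7.74 lb at month 6.

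Only the averaged group effect comes close to 6.6 lb. The same formula gives 0.231, 0.223 and 100.1 for the stated 0.23, 22% and 100 minutes/week. It does not reproduce the 375 calories (it gives 327.5). For weight, then, the power section appears to place the treatment effect in the group term on change scores.

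**Step 3. What the interaction holds if the outcome is weight loss at 3, 6 and 12 months.** Let δ₃, δ₆ and δ₁₂ be the TECH minus STND differences. With month 3 as reference, the group coefficient is δ₃ and the interactions are δ₆ − δ₃ and δ₁₂ − δ₃. If all three equal δ and adherence explains all of it, the group coefficient goes from δ to 0, and the interactions are 0 both before and after.

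**Step 4. Numerical check under the codings the text allows.** The scenario is an assumption and not a figure from the article: 20,000 subjects in two arms, adherence 0.2 higher in TECH, and 20 lb of loss per unit of adherence at every visit. The mediated effect is therefore 0.2 × 20 = 4 lb, constant over visits. Fitted by least squares on complete data with nominal time.

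| Coding | Group term, without → with adherence | Interactions without | Interactions with |
|---|---|---|---|
| A. Loss at 3/6/12 | 3.96 → −0.05 | 0.04, 0.01 | 0.04, 0.01 |
| B. Weight at 0/3/6/12, adherence 0 at baseline | −0.08 → −0.08 | −3.96, −4.00, −3.97 | 0.05, 0.01, 0.04 |
| C. Weight at 0/3/6/12, adherence as one time-invariant main effect | −0.08 → 2.92 | −3.96, −4.00, −3.97 | −3.96, −4.00, −3.97 |
| D. Weight at 0/3/6/12, adherence crossed with time | −0.08 → −0.09 | −3.96, −4.00, −3.97 | 0.04, 0.00, 0.07 |

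The criterion recovers the effect in B and D and misses it in A and C.

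**Step 5. Which coefficient.** Three groups by nominal time give (3 − 1) × (3 − 1) = 4 interaction coefficients with three visits, or (3 − 1) × (4 − 1) = 6 with four time levels. The section speaks of a single coefficient.

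**The case against.** The strongest defence is that Study design includes baseline as a time level. With baseline as reference, a constant advantage at follow-up is itself the group-by-time effect, and using the interaction as the treatment effect is then coherent. Codings B and D confirm this. The defence stands, so a reader who infers that the criterion always misses a constant mediated effect goes further than the article supports. It does not remove the problem: the mediation section says that the model predicts weight loss, the power section fits a group effect on change scores, and coding C fails even with baseline included.

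A reader might also infer that goal attainment has been dropped from the aim. The documents do not support that either. It is named three times, and incomplete wording in the model sentence is the likelier explanation. The sentence still specifies the analysis and is still too narrow.

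A third tempting inference is that baseline and month 12 rows must fall out of the model with adherence, because adherence is measured only at months 3 and 6, so that the two coefficients are not comparable. That holds only if adherence enters as a visit-specific covariate with missing values. The article does not say so, and codings B and D lose no rows.

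Finally, the simulated effect is exactly constant by construction, and nothing in the article says the real one will be. If it varies, coding A captures only the part that differs between visits.

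**Conclusion.** The mediator mismatch holds without assumptions: the model sentence omits goal attainment, which the abstract, the second aim and the section's own hypothesis all name.

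The fault in the criterion is conditional. If the outcome is weight loss at 3, 6 and 12 months, the criterion misses the whole of any mediated effect that is constant over visits: all 4 lb in the illustration. If weight is modelled over four time levels with baseline as reference, the criterion works when adherence is time-varying or crossed with time, and fails when adherence is one time-invariant main effect. The article states neither the reference level nor how adherence enters. The 4 lb is illustrative; the pattern follows from the algebra in Step 3. The point concerns the second aim only and changes neither the sample size nor the primary comparison of weight loss.

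**What to change.** - Enter goal attainment in the model alongside self-monitoring adherence: calorie and fat goal attainment from the dietary recalls (months 3 and 6, STND and TECH only) and accelerometer minutes of activity.
- State the outcome and the reference time level.
- Define the mediated effect as the change in the TECH vs STND weight-loss contrast at a named visit, with and without the mediators. Month 6 is one example: it is the last visit with adherence data, and the contrast is already the second planned Helmert contrast there.
- Fit both models to the same participants and rows, and bootstrap that difference.

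The cost is a change of wording and a little more analysis; every variable is already to be collected. The downside is that the mediation result is restricted to TECH vs STND and to visits with mediator data, so it will not cover SELF or month 12.

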#### Telephone screening

The telephone screen will review details of the study and review additional eligibility criteria including health status and medication use. Eligible and interested participants will be invited to attend a study orientation session and will be instructed to begin a one-week run-in period of dietary self-monitoring. If participants indicate a health condition such as type II diabetes or hypertension, medical clearance from a physician will be required prior to the pretreatment session in order to continue participation.

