#### In-person orientation session

During the orientation session, complete details of the study will be given and an equipoise induction will be performed to ensure that participants are aware of the pros and cons of the treatment conditions and to minimize the risk of differential attrition
[31]. Participant questions will be answered and informed consent will be obtained from interested participants. Consented participants will complete the final in-person screening and baseline assessment, which includes assessing blood pressure and anthropometric measurements. In addition, participants will complete a smartphone competency task to evaluate their ability to use basic functions of a smartphone after instruction and will complete a brief interview to assess: binge eating disorder, bulimia nervosa, substance abuse and dependence, attention deficit hyperactivity disorder, and major depressive disorder. Eligible participants will also complete baseline questionnaires and wear an accelerometer for 10 days to measure current activity levels.

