### Randomization

Eligible participants will be scheduled for a group time and assigned to a team with seven other participants, all of whom will be randomized to the same condition. Group randomization will be completed by a statistician, and neither participants, nor coaches, will find out group assignment until the first group session. The intervention timeline is presented in Figure
2.

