### Data analytic plan

#### Linear mixed modeling

Data will be analyzed on an intent-to-treat basis. The basic modeling approach will entail linear mixed models for longitudinal data. The primary aim is to test for treatment group differences on weight loss at 3-, 6-, and 12-months as well as differences in behavioral adherence and goal attainment at 3- and 6-months. Linear mixed models do not require that participants are measured at all time points, and therefore can include participants with missing data across time. In these analyses, we will examine changes across time by treating time as a nominal variable in the analysis to allow for non-linear trends. In addition to the effect of time, the main independent variable is treatment groups, a between-subjects factor with 3 levels: STND, TECH and SELF. A priori Helmert contrasts
[38] will be used to test the following comparisons at 3- and 6-months: 1) STND and TECH vs. SELF and 2) TECH vs. STND. We will also examine group by time interactions to test whether change in outcome across time differs by group.

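### The mediation analysis names no pre-randomisation covariate, so a common cause of recording and weight loss can appear as mediation whenever TECH raises adherence

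*Protocol article*

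**What the plan says.** The Linear mixed modeling section sets out the parent model: "In addition to the effect of time, the main independent variable is treatment groups, a between-subjects factor with 3 levels: STND, TECH and SELF". Time is nominal, and group-by-time interactions are examined. Study design lists four levels of time, with baseline as one of them.

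The Mediation analysis section then fits a model "similar to the model described above, but now including in the regression equation the potential mediating variables corresponding to adherence to self-monitoring". The group-by-time coefficients with and without adherence are compared, and the section says of the comparison: "This difference provides an estimate of the extent to which adherence may mediate the effects of the experimental condition on weight loss". On uncertainty it says: "Bootstrapping will be used to estimate the sampling variability of the mediation effect". Neither section names a baseline covariate or an assumption about common causes of adherence and weight loss.

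Some information on participants arises before anyone knows their arm. After the telephone screen, candidates "will be instructed to begin a one-week run-in period of dietary self-monitoring". At orientation, "Eligible participants will also complete baseline questionnaires and wear an accelerometer for 10 days to measure current activity levels". Under Randomization, "neither participants, nor coaches, will find out group assignment until the first group session". The mediation section mentions none of this information.

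**The concern.** Randomisation protects the effect of group on adherence and the effect of group on weight. It does not protect the association of adherence with weight, because participants themselves decide how many days to record. Someone more motivated or better organised is likely to record more and also to lose more weight for other reasons. The adherence coefficient is then non-zero even if recording does nothing. When TECH also raises adherence, as the trial hypothesises, the group coefficient falls once adherence is added, and the plan reads that fall as mediation.

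The second aim is the trial's test of its self-regulation theory, and the error runs in favour of the theory. A bootstrap interval describes the sampling spread around the biased value and does not move it. The problem is separate from the precision of the treatment contrasts and from the time order of adherence and weight.

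**Working it through.** **Inputs (Protocol article, Sample size and power).** Weight-loss SDs are 8.4 lb at month 3 and 10.7 lb at month 6, correlation 0.86. Diet self-monitoring SDs are 0.31 and 0.34, correlation 0.93. Detectable TECH–STND differences are 6.6 lb and 0.23, with 30 per group and 80% power.

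**Reproducing the planning figures** (two-sided 5% assumed, mean of the two visits):
- Weight: SD = √[(8.4² + 10.7² + 2 × 0.86 × 8.4 × 10.7)/4] = 9.21 lb. Detectable difference = (1.960 + 0.842) × 9.21 × √(2/30) = 6.67 lb, against 6.6 stated.
- Adherence: SD = √[(0.31² + 0.34² + 2 × 0.93 × 0.31 × 0.34)/4] = 0.319. Detectable difference = 2.802 × 0.319 × √(2/30) = 0.231, against 0.23 stated.

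Both agree, so the figures give a usable scale. They are detectable differences, not predicted effects.

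**Set-up for the bias.** Adherence has no effect on weight. TECH raises adherence by a = 0.23 at both visits. A stable trait correlates ρ with adherence and with weight loss within arm. The value of ρ is an assumption; the protocol gives none. True mediation is zero, so any mediated effect found is spurious.

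**Month 6 alone.** The within-arm slope of weight loss on adherence is b = ρ² × 10.7/0.34, and the spurious effect is 0.23 × b:
- ρ = 0.3: 0.65 lb, 10% of 6.6
- ρ = 0.5: 1.81 lb, 27%
- ρ = 0.6: 2.61 lb, 39%

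**Mixed model of months 3 and 6.** The response is weight loss since baseline, baseline is the reference level of time, and the covariance is unstructured. The generalised least squares slope is b = tr(V⁻¹C)/tr(V⁻¹S_M). Here S_M is the within-arm covariance of adherence over the two visits. C is the adherence–weight covariance, with entries ρ² × SD_M × SD_Y. V is the residual covariance of weight loss after adherence, found by iteration. The fall in each group-by-time coefficient is 0.23 × b:
- ρ = 0.3: 0.23 × 1.75 = 0.40 lb, 6% of 6.6
- ρ = 0.5: 0.23 × 4.98 = 1.15 lb, 17%
- ρ = 0.6: 0.23 × 7.40 = 1.70 lb, 26%

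A simulation with 30 per arm (800 trials per setting) gave falls at months 3 and 6 of 0.41 and 0.42, 1.15 and 1.15, and 1.72 and 1.71 lb. At ρ = 0 both were about zero. The mixed model gives less bias than month 6 alone because it also draws on within-person change, to which a stable trait contributes little.

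**What a covariate would remove.** Suppose a pre-randomisation proxy for the trait with reliability 0.5 (assumed), interacted with time, is in both models. The mixed-model figures become 0.21, 0.65 and 1.02 lb at ρ = 0.3, 0.5 and 0.6, so 48%, 43% and 40% of the bias is removed.

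**The bootstrap.** A percentile-interval check was run in a simpler regression on the mean of the two visits, where the bias is 0.60, 1.66 and 3.25 lb at ρ = 0.3, 0.5 and 0.7. The interval excluded zero in about 9%, 41% and 81% of runs, against 5% at ρ = 0. The mixed-model bias is smaller, so these rates only illustrate the pattern.

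**The case against.** **This is a condensed article, and covariates may be in an analysis plan that is not shown.** This stands as a limit on wording. A reader might infer that the mediation model will be unadjusted, but the text supports only that none is named. The parent model calls treatment the main independent variable, and the mediation model is only said to be similar to it, so covariates are not excluded. The point survives because the article does more than leave detail open: it fixes the estimator and its interpretation. Saying that adherence may mediate is a caution, not an identifying assumption.

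**The plan's quantity is a group-by-time coefficient, not an effect averaged over visits.** If time had only months 3 and 6 as levels, the interaction would hardly move: one run gave −0.095 without adherence and −0.092 with it. But Study design makes baseline a level of time, and with baseline as reference the month 3 and month 6 interactions fall by the amounts shown.

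**Useful covariates are not documented as available.** This also stands. A reader might infer that run-in counts and motivation scores are already in hand. The article says that participants are told to start recording, not that the records are returned, scored or kept, and it does not say what the questionnaires measure. Run-in days may also vary little among people selected as willing to self-monitor. Baseline accelerometer activity is the one measure clearly collected.

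**Unmeasured confounding is a general limit of mediation analysis, and its size rests on an assumed ρ.** Both are true. That is why a range is given and why a stated assumption and a sensitivity analysis are requested alongside the covariates.

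**Conclusion.** The concern holds in a limited form. As described, the mediation estimate is open to confounding of the unrandomised adherence–weight path, and nothing named in the plan addresses it. With no true mediation, the spurious effect is about 0.4 to 1.7 lb (6% to 26% of 6.6 lb) in the mixed model, or 0.65 to 2.6 lb (10% to 39%) at month 6 alone. These figures assume ρ between 0.3 and 0.6, a stable trait, and a TECH effect on adherence of 0.23. If TECH does not change adherence, the expected bias is zero.

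A reader might go further and infer that the analysis will usually find mediation whatever the truth. The figures do not support this: in the bootstrap check, false positives passed half of runs only at ρ = 0.7, above the range used here. The comparisons of weight loss between arms are not affected.

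**What to change.** Put the same pre-randomisation covariates, interacted with time, in both mediation models, with and without adherence:
- baseline accelerometer activity;
- days recorded in the run-in week, if those records are kept;
- any baseline questionnaire score that measures motivation or self-regulation.

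Add baseline weight only if the response is change from baseline and baseline is not also a level of the outcome; otherwise it would enter on both sides of the model. The sponsor should confirm which of these measures exist.

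State the no-unmeasured-confounding assumption. Report with the indirect effect how large a residual correlation between the adherence and weight errors would reduce it to zero.

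The cost is analysis-plan wording, retention of the run-in counts where possible, a few degrees of freedom, and perhaps a smaller reported indirect effect. No new visit or participant is needed. Confounding that the covariates measure poorly, or that arises after randomisation, will remain, and the sensitivity analysis is there to show how much it could matter.
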